### Data analysis

The primary analysis will be based on intention to treat (ITT), including all children residing in the intervention area as the exposed group. All available data up to the time of censuring (e.g., loss to follow-up, withdrawal, death, or study completion), irrespective of whether the child received any, part, or all the intended PMC doses. An additional per-protocol analysis will be completed which includes children who received at least one dose, all doses, or specific doses of PMC. The period of protection provided by SP is up to one-month post treatment and thus will constitute the protective window of those receiving the intervention. Data for both countries will be combined for analysis as well as assessed separately to ensure context specific nuances are fully assessed.

Incidence rates for malaria and anaemia will be calculated using multivariable Poisson regression, difference-in-difference, and interrupted time-series models comparing intervention and control areas [14–16]. Incidence rates, rate differences, and rate ratios between intervention and control area will be calculated for the ITT and per-protocol analysis. Malaria incidence will be determined by the number of malaria cases confirmed by either RDT or microscopy identified in either the passive or active cohort. Person-time at risk for each study outcome will be calculated based on the date of recruitment into the study population until the date of censuring or study end. For children who leave the study prior to the end date, the date of exit will be the date where they moved, withdrew from the study, or died. If that date is not known, the midpoint between the date of last contact and the date the loss was detected will be used. Protective effectiveness will be calculated for the intervention period including the 18 months of follow-up for the periods where PMC doses differ, stratified by first and second year of life, as well as during the post-intervention period, starting at 24 or 18 months of age in Cameroon and Côte d’Ivoire, respectively, to estimate any potential rebound in malaria.

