Where there are repeated measures per child, random effects or generalising estimating equations models will be used to adjust for non-independence of the data from the same individual. Regression models will assess factors associated with incidence of malaria infection including demographic variables, malaria history, reported vector control use, socio economic position, amongst others [17]. Transmission intensity, type of PMC delivery mode, impact of the estimated protective window of SP, and other factors will be adjusted for to assess their impact on the incidence trends [18]. Subgroup analysis will constitute assessing the impact of distance to the health facility as a proxy for access to health services according to the study endpoints highlighted above. Distance will be assessed according to tertials of distance of all study participants to their nearest health facility and as a continuous variable. Alternate model forms including interaction terms as well as semiparametric approaches to account for time-varying intervention effects to account for the expected 4-week prophylactic period of SP will be tested [19]. Because of the challenges in confirming cause of death in those who die in the community and the assumption that severe malaria cases will seek care at a health facility, only the passive cohort data will be used to assess these secondary outcomes [20]. An interim analysis will be conducted after the 4th active cohort visit and the study will be reported according to the ‘Strengthening the reporting of observational studies in epidemiology’ (STROBE) guidelines [21].

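### Per-protocol groups depend on doses received after recruitment, yet person-time starts at recruitment: selection and time-zero bias of uncertain direction

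*Protocol article*

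**What the plan says.** All of the following is in the protocol article, section Data analysis, unless noted.

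- Primary analysis: "The primary analysis will be based on intention to treat (ITT), including all children residing in the intervention area as the exposed group", whatever doses a child received.
- Additional analysis: "An additional per-protocol analysis will be completed which includes children who received at least one dose, all doses, or specific doses of PMC".
- SP protection: "The period of protection provided by SP is up to one-month post treatment". The article calls this the protective window.
- Contrast: "Incidence rates, rate differences, and rate ratios between intervention and control area will be calculated for the ITT and per-protocol analysis".
- Clock: person-time for each study outcome is "calculated based on the date of recruitment into the study population until the date of censuring or study end". No different start is given for the per-protocol set.
- Adjustment: "Transmission intensity, type of PMC delivery mode, impact of the estimated protective window of SP, and other factors will be adjusted for". The sentence goes on to give the purpose, which is to gauge how these factors affect incidence over time.
- Time-varying models for the four-week prophylactic period are listed among alternate model forms to be tested.

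Under Overview of PMC intervention and Aims and objectives, the standard of care is five SP doses in Cameroon and none in Côte d'Ivoire. The secondary objectives include the number and timing of doses and any dose response.

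**The concern.** A child enters the all-doses group only by staying resident, in follow-up and willing to attend until the last dose, yet the time counted for that child runs from recruitment. Time before a dose is pooled with time after it. Anything during follow-up that makes a child miss a dose also moves that child's whole record out of the group.

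The control side does not mirror this selection. Côte d'Ivoire controls have no doses to be selected on, so dose-completers face unselected children. In Cameroon a dose restriction could be applied in both areas, but receiving at least one dose does not separate them, and completing eight doses is a different hurdle from completing five.

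These results carry the secondary objectives on dose number, timing and dose response. The Discussion presents the question of which doses protect most as evidence for national programmes.

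A related ambiguity is that SP-window status and delivery mode follow from the intervention. If they entered the model for the total area effect, they would absorb part or all of that effect.

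**Working it through.** No figure in the article is at stake, so there is none to reproduce. The check is a simulation of the rules as written.

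**Inputs from the article**
- Follow-up of 18 months (Active cohort) and 20% loss (Sample size).
- Recruitment age 6–9 months in Cameroon and 10 weeks to 6 months in Côte d'Ivoire (Table 1).
- Malaria rates of 0.597 and 0.572 per child-year (from 597 and 572 per 1000 under-fives, Study site).
- SP window of one month (Data analysis).

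**Assumptions, not in the documents** (the schedule figure is not shown)
- Dose ages of 2.5, 3.5, 9, 12 and 15 months in a Côte d'Ivoire-like case, and 9, 12, 15, 18 and 24 months in a Cameroon-like case.
- 70% uptake per dose, and SP efficacy in the window of 0% or 80%.
- Probability that malaria in the previous month causes a missed dose: 0, 0.5 or 1.
- Recurrent Poisson malaria at a constant rate, with 200,000 children per scenario.
- All doses means every scheduled dose falling within the child's planned follow-up. The comparator is an unselected, undosed child.

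**Real effect, dosing unrelated to malaria (Côte d'Ivoire-like, 80% efficacy)**
- In the group with at least one dose, 25.4% of person-time precedes the first dose, and the ratio after the first dose is 0.857.
- Expected ratio with the clock at recruitment: 0.254 × 1.00 + 0.746 × 0.857 = 0.893. Simulated: 0.892. The misalignment dilutes the effect.

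**No SP effect: ratio in the all-doses group**

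| Case | Chance that recent malaria causes a missed dose | Clock at recruitment | Clock at first dose |
|---|---|---|---|
| Côte d'Ivoire-like | 0 | 0.99 | 1.00 |
| Côte d'Ivoire-like | 0.5 | 0.92 | 0.93 |
| Côte d'Ivoire-like | 1 | 0.81 | 0.83 |
| Cameroon-like | 1 | 0.74 | 0.76 |

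Moving the clock to the first dose barely helps. The group with at least one dose is little affected (0.99 and 1.00 when the chance is 1). In those same two chance-1 scenarios, classifying time by window status as it occurs gives in-window ratios of 1.00 (Côte d'Ivoire-like) and 1.01 (Cameroon-like), so time-updating removes the artefact.

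**Selection on remaining in follow-up.** In the Côte d'Ivoire-like case with no link and no effect, mean follow-up is 17.7 months among the fully dosed and 6.8 months among the undosed. For an outcome that ends follow-up, this is immortal time.

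**Conditioning on the window (Côte d'Ivoire-like, 80% efficacy).** The simulated area ratio is 0.897, with 0.20 inside the window and 1.00 outside it. The share of time in the window is (1 − 0.897)/(1 − 0.20) = 0.129, and 0.129 × 0.20 + 0.871 × 1.00 = 0.897. All of the area effect lies in the window term, so an area coefficient adjusted for window status would be 1.00.

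**The case against.** The case on the other side has five parts.

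- **The primary analysis is by area and ignores doses.** This stands in full: the dose selection does not reach it.
- **Malaria recurs and does not end follow-up.** An episode does not by itself prevent a later dose, and the eligibility criteria under Overview of PMC intervention do not list malaria as a reason to withhold one. This also stands. With no link between malaria and dosing, the null ratio is 0.99. Spurious protection needs such a link, or better-off children completing more doses, and the article does not establish either.
- **The one-month window directly follows the per-protocol sentence, time-varying models are foreseen, and the analysis plan is not shown.** This softens the point but does not remove it. Neither element is said to replace the recruitment-based clock, which the article states for every outcome without exception.
- **The adjustment sentence may describe an explanatory model.** A reader might infer that the main result will be adjusted towards no effect. The text does not support that: the stated purpose fits a model of what drives incidence, and nothing places these terms in the primary effect model. What stands is that nothing keeps them out either.
- **Mortality.** A reader might infer very strong spurious protection against death. If the last dose fell at the stated start of the post-intervention period (24 and 18 months), active-cohort children would have on average 1.5 and 4.15 of 18 months left, so null all-doses ratios of about 0.08 and 0.23. With a last dose three months earlier these become 4.5/18 = 0.25 and 7.15/18 = 0.40. The documents do not support these as estimates for this study. Deaths are assessed in the passive cohort, which enrols children up to 36 months. Deaths without a confirmed cause are excluded, no per-protocol mortality analysis is named, and the last-dose age is assumed. They only illustrate the mechanism.

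**Conclusion.** The concern holds for the additional per-protocol analysis and the dose-response results drawn from it. Followed as written, the article selects on doses received after time zero and compares the selected children with controls who are not selected in the same way.

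For malaria the direction is uncertain. A real effect is diluted (0.89 against 0.86) if dosing is unrelated to malaria, and a null effect reads as 0.92 to 0.74 in the all-doses group if recent malaria causes half or all of the affected doses to be missed. These sizes rest on assumed dose ages, uptake and efficacy, and on an unselected comparator. The Cameroon-like 0.74 would shrink to the extent that a matching restriction on controls cancelled the selection. Differences in access were not simulated; if children with poorer access miss more doses and have more malaria, spurious protection would again follow. For any outcome that ends follow-up, immortal time is added.

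Over-adjustment is a conditional risk that needs one clarifying sentence. It is not an established error.

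**What to change.** 1. In the per-protocol and dose-response analyses, replace the fixed groups by time-updated exposure. Split each child's follow-up at every recorded dose date. Classify child-time by doses received so far and by whether it lies within or beyond one month of the last dose. Compare it with control-area child-time of the same age and calendar month, adjusted for baseline covariates. In Cameroon, classify control-area doses in the same way.
2. State that SP-window status and delivery mode enter only these explanatory models, and not the model for the total intention-to-treat area effect.
3. Report the result as an observational dose-exposure analysis. Time-updating removes the time-zero problem, but not confounding by access or underlying risk.

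The cost is extra data preparation and modelling in a secondary analysis. No new data are needed: the Passive cohort section already has the date and the interventions given recorded at each contact.

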### Aims and objectives

This is a multi-site study with the primary aim to evaluate the impact of routine delivery of PMC on malaria incidence during the first two years of life. In Cameroon we will compare the effect of up to eight versus the standard of care of five doses, whilst in Côte d’Ivoire we will compare the effect of five versus zero SP doses, as the standard of care. Secondary objectives include determining any differences in: (i) severe malaria, malarial deaths, anaemia, and severe anaemia; (ii) differences in all indicators by country, delivery platform and the number and timing of doses; and (iii) any dose response effect or differences according to distance to the health facilities, as a proxy for access to care.

Evaluation of malaria interventions requires knowledge of the regional epidemiology of malaria and active and passive surveillance methods have been proposed for malaria vaccine efficacy studies. Passive case detection methods are limited to those seeking health care and are likely to underestimate burden of malaria in the community but may provide information on the clinical presentation and management of malaria relevant for planning health services. In contrast, active surveillance methods can minimise the effect of health care-seeking behaviour on malaria detection and measures of effect. It also allows for understanding the age, spatial and temporal patterns of disease in community settings. To address these issues, we will employ two approaches to address the study objectives. First, we will develop a passive cohort, which will capture routinely collected health data as part of all child visits to participating health facilities in the selected study sites. Secondly, we will form and prospectively follow an active cohort of children who will be visited at their households every three months over the study period. Reported malaria and anaemia cases in children under 5 years from the 5 years prior to the start of the study will also be collected to ensure results can be interpreted within the context of the broader malaria transmission patterns at each site.

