### Cameroon

Soa and Mbankomo are peri-urban areas located on the north-eastern and south-western periphery of Yaoundé, respectively (Fig. 2). Both areas have an estimated population density of 1,235 people per squared km and 15% of the population is under 5 years of age. In total, there are 39 health facilities in Soa, 12 of which are public and 28 have active CHWs. Of the 39 facilities, 20 administer EPI services and are eligible for SP administration as part of the expanded PMC programme. In Mbankomo, there are 32 health facilities, of which 4 are public and 10 have active CHWs. Of the 32 facilities, 19 administer EPI services and are eligible for SP administration as part of the standard of care PMC programme. Malaria incidence in both Soa and Mbankomo was 597 cases per 1000 children under 5 in 2020 [12]. Malaria transmission is typically highest during the two rainy seasons, from March to June and from October to November.

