### Côte d’Ivoire

Séguéla and Kani are rural areas located approximately 500 km northwest of the capital city, Abidjan (Fig. 2). The estimated population density is 45.98 people per squared km (2021) and 18% of the population is under 5 years of age. In total, there are 42 health facilities in Séguéla, all of which are public and 33 of these have active CHWs. Of the 42 facilities, 41 administer EPI services and thus are eligible for SP administration as part of the expanded PMC programme. In Kani, there are 8 health facilities, all of which are public and have active CHWs. Of the 8 facilities, all administer EPI services and thus would be eligible for SP administration if any doses were given as part of a standard of care PMC programme. According to the NMP, malaria incidence in both Séguéla and Kani was 572 cases per 1000 children under 5 in 2020 with the peak typically from April to July during the rainy season.

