### Passive cohort

All children up to 36 months of age residing in enumerated households during the census will be eligible for inclusion in the passive cohort and enrolled upon provision of written informed consent from their primary caregiver (Table 1). Enrolled children will be passively monitored to record both EPI vaccinations and PMC visits as well as clinical visits for malaria and anaemia to the health facility and/or CHWs over the 18-month study period. Older children (24 to 36 months at baseline) are not eligible to receive the intervention but will be enrolled in this study activity for two reasons: first, the older children will serve as an internal control as it is assumed that they will experience a similar malaria transmission intensity but will not receive the intervention and, secondly, as children will be followed for 18 months information will be available on children who age-out of eligibility to assess any impact beyond when children are eligible to receive PMC. Children will not be censored according to age.

During the passive cohort recruitment, trained fieldworkers will record basic demographic information about the child, recent malaria cases, amongst other information. An anonymous and unique QR code with the participant ID linked will be attached to each child’s health and vaccination record books. This QR code will be used to identify children participating in the study when they interact with the health system and facilitate linking the data generated by the routine system on EPI, PMC or clinical visit, which are stored in separate registers, with the research activities. During recruitment, the national health ID number assigned to each child and written in the health and/or vaccination record books will be recorded. The names of children and primary caregivers will also be recorded to provide a means to verify that children present match ID numbers. This also serves as a back-up method to link health information data that is routinely collected in different registers. Caregivers will be encouraged to take children to the participating facilities or CHWs to receive EPI vaccinations or PMC or for any illnesses.

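### Malaria incidence pools passively and actively detected cases although access to passive detection may differ between the areas; the two sources should be estimated separately

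*Protocol article*

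**What the plan says.** The Aims and objectives section of the protocol article states a "primary aim to evaluate the impact of routine delivery of PMC on malaria incidence during the first two years of life". The Data analysis section then says how incidence is counted: "Malaria incidence will be determined by the number of malaria cases confirmed by either RDT or microscopy identified in either the passive or active cohort". Under Passive cohort, the passive source is "clinical visits for malaria and anaemia to the health facility and/or CHWs over the 18-month study period", so CHW contacts feed the count.

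The Study site section describes who is there to detect cases. For Cameroon, "there are 39 health facilities in Soa, 12 of which are public and 28 have active CHWs" (intervention area), whereas "In Mbankomo, there are 32 health facilities, of which 4 are public and 10 have active CHWs" (control area). For Côte d'Ivoire, Séguéla (intervention) has 42 facilities, "all of which are public and 33 of these have active CHWs"; in Kani (control) all 8 facilities are public and have CHWs.

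The article itself distinguishes the two methods. Aims and objectives says that passive detection reaches only those who seek care, and that "active surveillance methods can minimise the effect of health care-seeking behaviour on malaria detection and measures of effect".

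**The concern.** The count that answers the primary aim mixes a source applied identically in both areas (scheduled household testing) with one that depends on whether an episode is brought to a facility or CHW, tested and recorded. Each country has one purposively chosen intervention area and one matched control area, so randomisation does not balance that second probability. The adjustment described under Data analysis covers infection risk factors, transmission intensity, delivery mode and unspecified other factors. It does not name the chance of detection.

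If that chance differs by area, part of the difference is read as a PMC effect, or part of a real effect is hidden. The combined-country estimate and the between-country comparison, a secondary objective, would carry the same distortion. PMC itself may add to it: the Overview of PMC intervention has SP delivered partly by CHWs and through outreach, which could bring intervention families into more contact with people who diagnose malaria.

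**Working it through.** **Inputs from the article.** Facilities with active CHWs (Study site):

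| | Intervention | Control | Gap |
|---|---|---|---|
| Cameroon | 28/39 = 71.8% | 10/32 = 31.3% | +40.5 points |
| Côte d'Ivoire | 33/42 = 78.6% | 8/8 = 100% | −21.4 points |

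The expected rate ratios (Sample size) are 0.70 in Cameroon and 0.60 in Côte d'Ivoire. The Cameroon gap is large (Fisher p = 0.0009). The Côte d'Ivoire gap rests on 8 control facilities (p = 0.32).

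**Assumed inputs.** The article gives no detection probability. For illustration, facilities capture 50% of episodes everywhere, and an active CHW adds c = 10 to 20 percentage points. At c = 0 there is no bias.

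**All ascertainment passive.** Observed RR = true RR × (0.5 + c × CHW share, intervention) / (0.5 + c × CHW share, control).

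- Cameroon, c = 0.10: 0.70 × 0.5718/0.5313 = 0.753.
- Cameroon, c = 0.20: 0.70 × 0.6436/0.5625 = 0.801.
- Côte d'Ivoire, c = 0.10: 0.60 × 0.5786/0.6000 = 0.579.
- Côte d'Ivoire, c = 0.20: 0.60 × 0.6571/0.7000 = 0.563.

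**Half of ascertainment passive.** The same assumptions give a relative detection k = 0.6/0.5 = 1.2 to 0.7/0.5 = 1.4 where a CHW is active. With s = 0.5 the passive share where no CHW is active, observed RR = true RR × [1 + s × share(intervention) × (k − 1)] / [1 + s × share(control) × (k − 1)].

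- Cameroon, k = 1.2: 0.70 × 1.0718/1.0313 = 0.728.
- Cameroon, k = 1.4: 0.70 × 1.1436/1.0625 = 0.753.
- Côte d'Ivoire: 0.588 and 0.579.

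**Direction in Côte d'Ivoire.** The CHW shares alone would move the ratio slightly away from 1. Capture there would be 57.9% against 60.0% (c = 0.10) or 65.7% against 70.0% (c = 0.20). Extra PMC contacts (five doses against none) that raised intervention-area capture by 2.1 to 4.3 points would cancel this, and more would reverse it. In Cameroon (up to eight doses against five) both mechanisms point toward 1.

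**What the Cameroon shift means for the planned size.** The stated 26 + 9 facilities can be reproduced with the cluster formula for two rates. It uses a control rate of 0.597, 60 children per facility × 0.8 × 1.5 years = 72 child-years, and 0.25 read as a between-cluster coefficient of variation (the article calls it an intra-cluster correlation, which does not reproduce the figures). Control facilities = (1.96 + 0.84)² × [0.0306 + 0.0167/3] / 0.1791² = 8.8, and three times that is 26.5. Power at 0.70 is 0.80. With the control rate held at 0.597, power is about 0.72 at RR 0.728, 0.63 at 0.753 and 0.45 at 0.801.

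**The case against.** The strongest reply is that none of this is shown to happen.

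- **CHWs may replace facility visits rather than add detections.** This stands: with replacement only, the pooled count is not distorted. The documents do not settle it.
- **The shares describe all facilities in each district.** The study samples EPI facilities at random (20 of 39 and 19 of 32 in Cameroon offer EPI), CHW presence in the selected catchments is not reported, and the shares are not weighted by children. This also stands, so the percentages signal a possible imbalance and do not measure it.
- **Active-cohort visits follow the same procedures in both areas.** True, and this is why the half-passive figures are smaller. Pooling dilutes the protection without removing the problem.
- **The plan has safeguards.** It lists difference-in-difference and interrupted time-series models, collects up to five years of earlier routine data, and uses children aged 24 to 36 months at baseline as an internal control. These may remove detection differences that are stable over time or shared across ages. They would not remove extra detection created by PMC contacts, which begin with the programme and do not reach the older children. Distance to facility is analysed as a proxy for access, but it does not measure CHW presence. Which model leads, and the full covariate list, may be in an SAP that is not shown and are not criticised here.
- **PMC contacts may add little.** Most use existing immunisation and vitamin A visits. Fair: the extra contact is plausible, not documented.

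**Conclusion.** The point holds as a risk that the outcome definition creates and that separate reporting would expose. In Cameroon the plausible direction is toward no effect, provided that CHWs add detected cases and that the district-wide imbalance carries over to the sampled catchments. Under the assumed capture figures, a 30% reduction would appear as roughly 20 to 25% if all ascertainment were passive, and 25 to 27% if half were. In Côte d'Ivoire the shift from CHW shares is small and the net sign is undetermined.

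A reader might infer from 72% against 31% and 79% against 100% that the effect is biased in opposite directions in the two countries. The documents do not support that: they give no detection probability, the shares are not those of the sampled catchments, and in Côte d'Ivoire extra PMC contacts would work against the CHW gap. A reader might also conclude that active testing should become the sole primary outcome. That does not follow either. At most seven tests three months apart miss clinical episodes between visits, and the Active cohort section describes that measurement as malaria infection, so the quantity estimated would change.

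**What to change.** Do not rest the primary aim on one pooled count. Estimate and report the intervention-control rate ratio separately for:

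- **actively detected malaria**, meaning a positive RDT or microscopy result at a scheduled household visit. Schedule and tests are the same in both areas, and this is the cohort for which the sample size was calculated.
- **passively detected clinical malaria.** Adjust this model for the care-seeking answers collected in the census. In Cameroon, also adjust for whether the catchment has an active CHW, since both areas have facilities with and without them. This second adjustment is not possible in Côte d'Ivoire, where no control facility lacks CHWs.

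Add a sensitivity analysis restricted to facility-detected cases. If CHWs divert cases from facilities, this analysis errs the other way, so read it alongside the main passive result and not as a replacement. Confirm that the clinical-visit form records whether a facility or a CHW made the diagnosis; the Passive cohort section does not list this explicitly for clinical visits. Interpret the combined-country and between-country results according to whether the two sources agree.

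The cost is mainly wording and a little more analysis, with somewhat less precision for each separate estimate. Neither source suffices alone, so both should be kept.
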